#### *Analysis of matched data*

The matched set will be analysed using Poisson regression with generalized estimating equations to account for the matched-nature of the data. The outcome will be the event rate (e.g. rate of avoidable hospitalisations) occurring after the “matching-period”.

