### 2.2 Description of CDMP participants

We will describe baseline characteristics of CDMP participants overall and broken down by year of enrolment (2011, 2012 and 2013). Baseline characteristics will include:

- Age
- Gender
- Aboriginality
- ARIA
- SEIFA

- Source of referral
- Target condition(s)
- Risk of hospitalisation
- Special population flag
- Initial SF1
- Initial intervention
- Reasons for non-enrolment
- Referral target
- Program consent
- Data use consent
- Number of hospitalisations in 2010, average length of hospital stay, total hospital bed days
- Number of unplanned hospitalisations in 2010, average length of unplanned hospital stay, total unplanned hospital bed days
- Number of avoidable hospitalisations in 2010, average length of avoidable hospital stay, total avoidable hospital bed days
- Number of ED admissions in 2010 overall and by triage categories 1-5

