### 3 Evaluation of efficacy outcomes

#### 3.1 Efficacy outcomes

The primary efficacy outcome will be the rate of avoidable hospitalisations. Avoidable hospitalisations are defined as hospitalisations that fall under any of the following categories:

1. Vaccine-preventable:
  - "Influenza and pneumonia" (where any of the diagnosis fields have ICD-10-AM code as J10, J11, J13, J14, J15.3, J15.4, J15.7, J15.9, J16.8, J18.1, J18.8 excluding those where secondary diagnosis is D57)
  - "Other preventable vaccine" (where any of the diagnosis fields have ICD-10-AM code as A35, A36, A37, A80, B05, B06, B16.1, B16.9, B18.0, B18.1, B26, G00.0, M01.4)
2. Chronic:
  - "Diabetes complications" (where any of the diagnosis fields have ICD-10-AM code as E10.1-E10.8, E11.0-E11.8, E13.0-E13.8, E14.0-E14.8)
  - "Nutritional deficiencies" (where principal diagnosis has ICD-10-AM code as any of E40-E43, E55.0, E64.3)
  - "Iron deficiency anaemia" (where principal diagnosis has ICD-10-AM code as any of D50.1-D50.9)
  - "Hypertension" (where principal diagnosis has ICD-10-AM code as any of I10, I11.9)
  - "Congestive heart failure" (where principal diagnosis has ICD-10-AM code as any of I11.0, I50, J81)
  - "Angina" (where principal diagnosis has ICD-10-AM code as any of I20, I24.0, I24.8, I24.9)
  - "Chronic obstructive pulmonary disease" (where principal diagnosis has ICD-10-AM code as any of J41-J44, J47 or the principal diagnosis ICD-10-AM code is J20 with secondary diagnosis as J41, J42, J43, J44, J47)

- "Asthma" (where principal diagnosis has ICD-10-AM code as any of J45, J46)
3. Acute:
- "Dehydration and gastroenteritis" (where principal diagnosis has ICD-10-AM code as any of E86, K52.2, K52.8, K52.9)
  - "Convulsions and epilepsy" (where principal diagnosis has ICD-10-AM code as any of G40, G41, O15, R56)
  - "Ear, nose and throat infections" (where principal diagnosis has ICD-10-AM code as any of H66, H67, J02, J03, J06, J31.2)
  - "Dental conditions" (where principal diagnosis has ICD-10-AM code as any of A69.0, K02-K06, K08, K09.8, K09.9, K12, K13)
  - "Perforated/bleeding ulcer" (where principal diagnosis has ICD-10-AM code as any of K25.0-K25.2, K25.4-K25.6, K26.0-K26.2, K26.4-K26.6, K27.0-K27.2, K27.4-K27.6, K28.0-K28.2, K28.4-K28.6)
  - "Ruptured appendix" (where any of the diagnosis fields have ICD-10-AM code as K35.0)
  - "Pyelonephritis" (where principal diagnosis has ICD-10-AM code as any of N10, N11, N12, N13.6)

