### 3.2.4 *Adjusted analyses*

Both the before-after and the time-dependent analyses will be performed without and with adjustment. Potential covariates will include LHD, age, gender, aboriginality, ARIA, SEIFA, target conditions, SF1 and previous patterns of service utilisation (number of hospitalisations in 2010, number of unplanned hospitalisations in 2010, number of avoidable hospitalisations in 2010 and number of ED admissions in 2010).

Each potential covariate will first be analysed using a univariate Poisson regression and only those with a univariate p-value smaller than 0.20 will be included in the final model. To avoid problems due to colinearity, in case of two covariates with a Pearson correlation coefficient greater than 0.8, only the one with the smallest univariate p-value will be kept in the final model. For covariates with more than 10% of data missing, we will create a separate category labeled “missing”.

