## 3.3 *Analyses using a control group*

### 3.3.1 *Matched analyses*

The primary analysis for assessing the effect of the program will be performed using a propensity-matched cohort as the comparator.

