#### *Propensity scoring and matching*

Using baseline characteristics, we will calculate a propensity score defined as the probability of getting enrolled in the program. Matched controls will be selected from the APDC dataset using individuals who never got enrolled into the program. We will follow the following steps:

- Step 1:** Group program participants by period (e.g. month/quarter/semester) according to their enrolment date (the final “grouping period” will depend on the number of participants recruited).
- Step 2:** For each stratum/period, obtain details of the latest hospitalisation occurring in the 12 months preceding the period. Any program participant with no hospitalisation in the preceding 12 months will be excluded from propensity-based analyses.
- Step 3:** Within each stratum/period, calculate propensity score using a logistic regression modeling the probability of getting enrolled in the program. Covariates will include all variables considered for adjusted analyses.
- Step 4:** Within each stratum/period, starting with the earliest period, match 2 non-CDMP participants for each CDMP participant on the propensity score using optimal matching procedures. A control which has been used as a match in an earlier period is no longer available as match for a future period.
- Step 6:** Check the quality of the matching by plotting the propensity score distribution between the cases and controls overall and by period and by calculating the standardised difference for every covariate included in the propensity score calculation.

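### The primary matched outcome model names no covariate, so it gives up available precision and has no prespecified protection against imbalance left after matching

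*SAP*

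**What the plan says.** SAP section 3.1 sets the endpoint: "The primary efficacy outcome will be the rate of avoidable hospitalisations". Section 3.3.1 sets the comparison: "The primary analysis for assessing the effect of the program will be performed using a propensity-matched cohort as the comparator".

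Under 'Analysis of matched data' the model is given in one sentence, "The matched set will be analysed using Poisson regression with generalized estimating equations to account for the matched-nature of the data", and the response in the next, "The outcome will be the event rate (e.g. rate of avoidable hospitalisations) occurring after the" matching period. Neither sentence names a covariate.

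Section 3.2.4 provides adjustment for the cohort analyses: "Both the before-after and the time-dependent analyses will be performed without and with adjustment". Its list of potential covariates ends with "number of avoidable hospitalisations in 2010 and number of ED admissions in 2010". Step 3 of 'Propensity scoring and matching' puts the variables of that list into the propensity score. Step 6 checks balance with score plots and "by calculating the standardised difference for every covariate included in the propensity score calculation". The sensitivity analyses for the matched comparison vary only the baseline period.

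**The concern.** Earlier use of hospital is usually a strong predictor of later use, and the plan already assembles it for the score. Leaving it out of the outcome model has two possible costs.

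- **Precision.** Variation between people that the baseline count could explain stays in the error, which widens the interval around the primary rate ratio.
- **Protection.** Matching on a scalar score balances covariates on average. Two people with the same score can have different admission histories, offset by age, region or other terms. Step 4 states no caliper and uses each control once, so close matches are not guaranteed. If Step 6 shows imbalance, the SAP gives no threshold and no response. The imbalance would then either pass into the primary estimate or prompt a modelling choice made after the data are seen.

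The before-after and time-dependent analyses have a prespecified adjusted version. The primary analysis does not.

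**Working it through.** **1. What the SAP fixes.** Matching is 2:1 on the score, by optimal matching within enrolment period. The model is a Poisson GEE on the post-period rate. The SAP gives no sample size, event rate, overdispersion, baseline-to-outcome correlation or size of the control pool. There is therefore no stated figure to reproduce, and every numerical input below is an assumption.

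**2. Imbalance in a measured covariate.** With a log link and a true rate ratio of 1, the unadjusted rate ratio is about exp(β × d). Here d is the residual standardised difference and β the change in log rate per SD of the covariate.

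| β | d = 0.05 | d = 0.10 | d = 0.20 |
|---|---|---|---|
| 0.2 | 1.01 | 1.02 | 1.04 |
| 0.4 | 1.02 | 1.04 | 1.08 |
| 0.6 | 1.03 | 1.06 | 1.13 |

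**3. A harsher case: imbalance in underlying risk.** Let the annual rate be μ and the gamma frailty variance φ, with one year of baseline and one of follow-up. If participants' underlying rate is raised so that the baseline count differs by d SDs, the expected unadjusted rate ratio is 1 + d × √(μ + φμ²)/μ. For μ = 0.6, φ = 1, d = 0.1 this is 1 + 0.1 × 0.980/0.6 = 1.163.

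A simulation (500 participants, 1,000 controls, 30 replicates, Monte Carlo error about 0.02 on the log scale) gave, at d = 0.1:

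| μ | φ | Expected | Unadjusted | Adjusted for baseline count | Share of log bias removed |
|---|---|---|---|---|---|
| 0.3 | 1 | 1.208 | 1.259 | 1.198 | 22% |
| 0.3 | 2 | 1.231 | 1.266 | 1.172 | 33% |
| 0.6 | 1 | 1.163 | 1.159 | 1.085 | 45% |
| 0.6 | 2 | 1.191 | 1.181 | 1.081 | 53% |

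The last column is 1 − ln(adjusted)/ln(unadjusted). Adjustment helps in every row, but an observed count is an imperfect measure of risk and removes only part of the bias.

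**4. Does matching leave such imbalance?** That depends on the supply of controls. In simulations of 2:1 nearest-score matching without replacement, with the baseline count in the score and a true rate ratio of 1:

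| Population | Participants | Unadjusted rate ratio |
|---|---|---|
| 9,600 | 600 | 1.01 to 1.05 |
| 9,600 | about 1,200 | 1.02 and 1.07 in one set of runs; 1.09 to 1.24 in another |
| 9,600 | about 2,400 | 1.09 and 1.24 |
| 60,000 | about 1,200 | 1.005 |
| 100,000 | 1,200 | 1.002 to 1.003 |

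The spread at about 1,200 participants shows how far the answer turns on the assumed inputs.

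**5. Precision.** The measure is the variance of the log rate ratio, adjusted over unadjusted.

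- With no imbalance, in the setting of step 3 (controls drawn at random, not matched on the count), the ratios were 0.95, 0.87, 0.85 and 0.70. The last is (0.0882/0.1055)². The transformation used there, log(count + 1/φ), suits the assumed frailty model exactly, so these gains are on the favourable side.
- After matching from the 60,000 population, the variance fell by about 11% and 21%.
- After matching from the 100,000 population, the ratios were 0.95 and 0.73, so 5% and 27% lower.
- At the extremes, one matched scenario showed no gain (1.01) and one a 44% reduction (0.56).

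**The case against.** The best defence is that matching is the plan's method of confounding control. The baseline count is in the score, Step 6 checks every score covariate, and analysing a matched set without further regression is a recognised design. Section 3.2.4 belongs to the cohort analyses, so its silence on the matched set is not an exclusion. All of this stands. It makes the point an improvement to the plan, not the repair of an error.

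The step list jumps from 4 to 6, so a missing step might have dealt with imbalance. Any response to the balance check would have to follow that check, however, and nothing follows Step 6 except the unadjusted model and the change of baseline period.

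A reader might infer that the primary rate ratio is biased by several per cent, or that the program will look worse than it is because controls run out among the sickest. The documents do not support either. Section 1.2 describes the APDC as covering every public and private admission in NSW, controls come from everyone never enrolled, and the SAP gives no sign of scarcity. Material bias appeared only with small assumed populations.

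A reader might also apply the usual factor 1 − ρ² to claim a set gain in power. That factor overstates the gain here. At ρ = 0.43 it gives 1 − 0.43² = 0.815, where a matching simulation gave 0.94. At 0.48 it gives 0.77 against 0.95, and at 0.69 it gives 0.52 against 0.73. The SAP also states no starting power. In addition, the counts in section 3.2.4 are for 2010, up to about three years before the last enrolments, so the real correlation may be lower than assumed.

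**Conclusion.** The point holds as a low-cost improvement. The primary model leaves out a predictor that the plan already collects for the score, and the plan has no prespecified response to imbalance that it will itself measure.

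A precision gain is likely but variable: roughly 0 to 30% lower variance of the log rate ratio in most of the assumed scenarios, including those with a large pool and negligible bias. The size of any bias cannot be derived from the SAP, and neither its presence nor its direction should be asserted. Adjustment reduces residual confounding but does not fully remove it. These conclusions rest on assumed rates, overdispersion, enrolment models and pool sizes. What rests on the text alone is that the primary model names no covariate and that no step acts on the balance check.

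**What to change.** In 'Analysis of matched data', prespecify the primary model as a Poisson GEE clustered on matched set, with:

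- program status;
- the baseline avoidable-hospitalisation count over the same pre-period as the score, with its transformation stated in advance;
- the other score covariates held for both participants and controls.

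For each secondary count outcome, use that outcome's own baseline count in the same way. Keep the unadjusted matched model as a sensitivity analysis, so that the effect of adjustment can be seen.

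The cost is SAP wording and a few more model terms, with no new data beyond what the score requires. The rate ratio becomes conditional on the covariates. With a log link and no effect modification it is collapsible, so the target is unchanged.

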#### *Sensitivity analyses*

Sensitivity analyses using different baseline periods (e.g. 6 months or 2 years) will be performed to assess the impact on the size of the matched cohort as well as the results.
